
### Sample size

The PASS sample size software (version 11.0; NCSS, LLC, East Kaysville, UT, USA) was used to estimate the sample size needed for the current study based on the following formula: *N* = (1/Q1 + 1/Q2) [(*Z*_*α*/2_ + *Z*_*β*_)*σ*/*δ*]^2^. As the primary parameter, the implant survival rate was used to estimate the sample size. The mean 5-year survival rate and standard error (SE) were calculated as described in a previous study [21] (survival rate after 5 years = 97.8%; mean of paired difference [*δ*] = 5.0%; SE [*σ*] = 5.0%) with significance criteria of *α* = 0.05 (error) and *β* = 0.10 (type II error). A two-tailed, non-inferiority analysis was performed. To reach a power of 90%, at least 16 patients (32 sites) should be included. Assuming a dropout rate of 20%, 20 patients (40 sites) were needed. Considering the cluster effect caused by the split-mouth design, we further enlarged the sample size to 25 patients (50 sites) for this trial.

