#### Primary outcomes of the trial

The primary parameter of the current trial is implant survival rate, which will be calculated as the proportion of retained implants at 5 years of follow-up.

The criteria of survival or failure of an implant were referred to the consensus of the International Congress of Oral Implantologists [20]. The implant will be regarded as failed if any of the following happens: (a) pain on function, (b) mobility, (c) radiographic bone loss > 1/2 length of the implant, (d) uncontrolled exudate, and (e) no longer in the mouth. Otherwise, the implant will be regarded as surviving.

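### The sample size enters a 5% standard error where its formula needs the SD of a yes/no outcome, so the stated 90% power is unsupported; the printed inputs themselves give 42 sites, not 32

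*Protocol article*

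**What the plan says.** The primary outcome (Primary outcomes of the trial) is "implant survival rate, which will be calculated as the proportion of retained implants at 5 years of follow-up". Under Data collection and management, only one randomly chosen implant per side is evaluated, so each side of each patient contributes one yes/no result.

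The Sample size section says that software "was used to estimate the sample size needed for the current study based on the following formula" N = (1/Q1 + 1/Q2)[(Zα/2 + Zβ)σ/δ]². On the source of the inputs it says: "The mean 5-year survival rate and standard error (SE) were calculated as described in a previous study". The inputs are "survival rate after 5 years = 97.8"%, "mean of paired difference [*δ*] = 5.0"%, a standard error of 5.0% used as σ, "significance criteria of *α* = 0.05 (error"), and β = 0.10. The analysis is described as two-tailed and non-inferiority. The conclusion is "To reach a power of 90%, at least 16 patients (32 sites) should be included". This is raised to 20 patients for 20% dropout and to 25 for the cluster effect of the split-mouth design. No other margin and no within-patient correlation are given.

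**The concern.** In this formula σ is the SD of a single observation. On the paired reading it would be the SD of a single within-patient difference. A standard error measures the precision of a summary and depends on the size of the study it came from, so it cannot take that place. For a yes/no outcome σ is not a free choice, because the survival rate fixes it. The plan states both 97.8% and 5%, and they do not fit together.

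The primary hypothesis is that the modified procedure does about as well as the standard one. With survival near 98%, few failures are expected: if sites were independent, the chance of none in 50 is 0.978^50 = 33%. A result with no visible difference is therefore likely, and the 90% figure would invite readers to take it as a powered demonstration of non-inferiority.

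**Working it through.** **Inputs.** From Sample size: survival 0.978, δ = 0.05, σ = 0.05, two-sided α = 0.05 (z = 1.960), power 90% (z = 1.2816), 16, 20 and 25 patients. Assumed here: Q1 = Q2 = 0.5 (one side per arm), within-patient correlation ρ, true difference 0 and, where stated, δ read as the margin.

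**1. The plan's own figure.** With Q1 = Q2 = 0.5, 1/Q1 + 1/Q2 = 4, and σ/δ = 1.
- 90% power: N = 4 × (1.960 + 1.2816)² = 42.0 sites.
- 80% power: N = 4 × (1.960 + 0.8416)² = 31.4, rounded up to 32 sites.
- The printed 32 sites (16 per side) is the 80% answer. Power at 16 per side is 80.7%.
- The dropout step, 16/0.8 = 20, is correct.

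**2. The SD that the survival rate implies.**
- Per site: √(0.978 × 0.022) = 14.7%.
- Paired difference: √(2 × 0.021516 × (1 − ρ)) = 20.7% at ρ = 0, 14.7% at ρ = 0.5, 10.4% at ρ = 0.75.

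**3. Can σ = 5% hold for the paired difference?** The difference takes the values −1, 0 or +1.
- If δ = 5% is a true mean paired difference, as labelled, at least 5% of pairs are discordant and the SD is at least √(0.05 − 0.05²) = 21.8%. So σ = 5% is impossible.
- If δ is a margin and the true difference is 0, σ = 5% needs 2 × 0.021516 × (1 − ρ) = 0.0025, so ρ ≈ 0.94.

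**4. Power by normal approximation**, margin 5 points: Φ(0.05√n/SD − 1.960).

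| Pairs | ρ = 0 | ρ = 0.5 | ρ = 0.75 |
|---|---|---|---|
| 25 | 23% | 40% | 67% |
| 20 | 19% | 33% | 58% |

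For example, 25 pairs at ρ = 0: Φ(0.05 × 5/0.2074 − 1.960) = Φ(−0.755) = 22.5%.

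Pairs needed for 90%, (3.2415 × SD/0.05)²: 180.9, so 181, at ρ = 0; 90.4, so 91, at ρ = 0.5. For 25 pairs to give 90%, the SD must be 0.25/3.2415 = 7.7%, so ρ ≈ 0.86. At that value only 25 × 0.0771² ≈ 0.15 discordant pairs are expected in the whole trial, and a normal approximation means little.

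**5. Paired score (Tango) interval.** With no discordant pair the 95% lower limit for test minus control survival is −z²/(n + z²).
- 25 pairs: −3.84/28.84 = −13.3 points.
- 20 pairs: −3.84/23.84 = −16.1 points.
- Reaching −5 points without any failure takes 73 pairs.
- With 25 pairs, no test-side failure and 1, 2, 3 or 4 control-side failures, the limit is −9.9, −6.4, −2.9 or +0.5 points.
- Power enumerated over the discordant counts, 25 pairs, ρ = 0: about 1%.

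**The case against.** Several points on the other side have weight.

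- The text calls 5% a mean paired difference and never a margin. That stands: reading it as the margin is an inference, made because the calculation is described as non-inferiority and no other candidate is given. Neither the SD error nor the 42-site result depends on it.
- The source study is not at hand, so σ = 5% might be a mislabelled SD. Relabelling does not help, because 5% is incompatible with a yes/no outcome at 97.8% unless the two sides of a patient almost always agree. The section offers no such assumption and treats the pairing as a reason to enlarge the sample.
- Other routes come near 16. A one-sided 5% test gives 34.3 sites (18 per side), and a paired t test of 13 pairs with a Wilcoxon efficiency adjustment gives 13/0.864 = 15.05, so 16. Neither is the two-tailed printed formula.
- A reader might take 19% to 40% as the trial's actual power. The documents do not support that. The range depends on a correlation between 0 and 0.5 that they never state. Power is higher at 0.75, and the approximation would pass 90% above about 0.86. The score interval gives about 1% for the same design at correlation 0, so the two methods should not be merged into one claim.
- A reader might also infer that −13 points is the best limit attainable, or that 5 points can never be met. Neither is so: three control-side failures with none on the test side would meet it.
- A plain Wald interval has zero width when no implant fails and would pass. That reflects a breakdown of the method and demonstrates nothing.
- The 20-pair figures assume that lost patients leave the analysis. The Missing data section counts drop-outs as non-survival, which keeps 25 pairs, so the 20-pair row is only a sensitivity figure.

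**Conclusion.** The point holds. That σ is wrong for this outcome follows from the plan's own survival rate, with no outside assumption: 14.7% per site against 5% entered. With Q1 = Q2, it is equally certain that the printed formula and inputs give 42 sites at 90% power and that 32 is the 80% answer.

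The size of the power loss is conditional. With a 5-point margin, true difference 0 and two-sided 5%, 25 pairs give about 23% to 67% for correlations from 0 to 0.75, by normal approximation. Under a paired score interval a failure-free result stops at −13.3 points. The design does not support a confirmatory reading at 5 points. This must be corrected, because it governs how the primary result will be read.

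**What to change.** In the Sample size section:

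- Delete the 90% power claim and the minimum of 16 patients derived from it.
- Present 25 patients (50 sites) as a size chosen for feasibility.
- State that 5-year survival will be estimated with a paired score 95% confidence interval for the difference, and will not be confirmed as non-inferior at 5 points.
- State that the lower limit would be about −13 points if no implant fails in 25 pairs. Word it as the limit in that case only, not as the best the trial could reach.
- Say whether the 5% is an expected difference or a margin, if it is kept at all.

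The cost is a rewording, with no added patients or visits, and it can be done while recruitment continues. The downside is that the trial's stated power becomes much less favourable and the primary claim more modest.

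### On the printed formula and inputs, 16 patients (32 sites) correspond to about 80% power; 90% needs 22 patients, and the clustering reason for enlarging to 25 is unsupported

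*Protocol article*

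**What the plan says.** The Sample size section says that PASS 11 "was used to estimate the sample size needed for the current study based on the following formula", and prints N = (1/Q1 + 1/Q2)[(Z_α/2 + Z_β)σ/δ]². The inputs follow: "survival rate after 5 years = 97.8" per cent; "mean of paired difference [*δ*] = 5.0" per cent; σ, labelled a standard error, also 5.0%; α = 0.05; and β = 0.10. On sidedness: "A two-tailed, non-inferiority analysis was performed".

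The result is then given: "To reach a power of 90%, at least 16 patients (32 sites) should be included". A 20% dropout allowance raises this to 20 patients (40 sites). The last step reads: "Considering the cluster effect caused by the split-mouth design, we further enlarged the sample size to 25 patients (50 sites) for this trial".

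Two other places bear on this. The Primary outcomes section defines the endpoint as the proportion of implants retained at 5 years. Data collection and management says that where a side has more than one implant, a single randomly chosen one is evaluated.

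**The concern.** Every term the formula needs is printed or follows from the design, so the result can be checked directly. It does not follow at the stated power. The stated power is the justification for the size of the trial on its primary outcome, and the dropout step is built on the same figure.

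The final enlargement raises a second question. Each patient contributes one test side and one control side, with one implant evaluated per side. It is not clear what clustering is left to inflate the sample, and the section gives no correlation or design effect from which 25 could be derived.

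**Working it through.** **Inputs.** From Sample size: δ = 5.0%, σ = 5.0% (so σ/δ = 1), two-sided α = 0.05 (Z = 1.960), β = 0.10 (Z = 1.282). Q1 and Q2 are not given values. I take Q1 = Q2 = 0.5, because the split-mouth design puts one side of each patient in each group; then 1/Q1 + 1/Q2 = 4. The 97.8% survival rate does not enter the printed formula.

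**Trying to reproduce the stated figure.**

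- At 90% power: N = 4 × (1.960 + 1.282)² = 42.03 sites, or 21.01 per side. In whole patients this is 22 (44 sites). The article states 16 (32 sites).
- At 80% power: N = 4 × (1.960 + 0.842)² = 31.40 sites, or 15.70 per side. In whole patients this is 16 (32 sites), exactly the stated figure.

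**Other readings at 90% power.**

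| Reading | Result | Gives 16 patients? |
|---|---|---|
| Q1, Q2 as unequal fractions summing to 1 | multiplier above 4, so more than 42.03 sites | no |
| N read as per side (Q1 = Q2 = 1) | 21.01 (15.70 at 80% power) | no |
| One-sided α = 0.05 | 4 × (1.645 + 1.282)² = 34.26 sites, 18 patients | no |
| One-sample paired z, σ as SD of the difference | (1.960 + 1.282)² = 10.51, 11 patients | no |
| Paired t, σ as SD of the difference | 13 patients | no |
| Two-sample t | about 22–23 per side | no |
| Non-inferiority of proportions, 97.8%, 5% margin | 181 per side (148 with one-sided 0.05) | no |

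**Power on the printed formula**, Φ(√(N/4) − 1.960), with N in sites:

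| Patients (sites) | Power |
|---|---|
| 16 (32) | Φ(2.828 − 1.960) = 80.7% |
| 20 (40) | Φ(3.162 − 1.960) = 88.5% |
| 25 (50) | Φ(3.536 − 1.960) = 94.2% |

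**Later steps.** 16/0.8 = 20 reproduces the dropout step, so it inherits the base figure. From 22 patients the same rule gives 22/0.8 = 27.5, rounded up to 28. Conversely, 25 × 0.8 = 20, so 25 enrolled patients with the assumed dropout leave 20, with 88.5% power.

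**Enlargement to 25.** 25/20 = 1.25, a factor with no stated source. If each side has SD σ and the two sides correlate at ρ, the within-patient difference has variance 2σ²(1 − ρ). The printed two-group formula corresponds to ρ = 0; a positive ρ lowers the variance. Evaluating one implant per side also removes clustering within a side.

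**The case against.** The 32-site figure cannot be rescued, but several points on the other side stand.

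- **The planned size is not 32 sites.** A reader might infer that the trial runs with a type II error of about 19%. The documents do not support that: 80.7% belongs to an intermediate figure, and the plan is for 25 patients. On the same inputs the gap at the final size is 90 − 88.5 = 1.5 points, and only if the full 20% drop out. Missing data also says that drop-outs are counted as non-survival, so they stay in the analysis; the 88.5% treats them as contributing nothing.
- **The paired reading is conservative.** δ is described as a paired difference. If σ is the SD of that difference, about 11 patients suffice and 16 give Φ(√16 − 1.960) = 97.9% power. This still does not yield 16 at 90%, but it means that a shortfall exists only under the two-group formula. That is the formula printed.
- **The corrected figure is not an adequate size.** A reader might take 42 or 44 sites to be sufficient. That holds only if 5.0% is a valid SD. It is labelled a standard error, and the outcome is binary. At 97.8% survival the binary SD is √(0.978 × 0.022) = 14.7%, and the same formula then gives about 42.03 × (14.7/5.0)² ≈ 362 sites. This is a separate problem, which the correction does not solve.
- **The enlargement does no harm.** Going from 20 to 25 cannot lower power. Only its reason is faulty. Nor should a (1 − ρ) factor replace it on present information: if σ already belongs to the paired difference, that would count the correlation twice.

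**Conclusion.** The stated size and the stated power do not match. On the printed formula with two-sided α = 0.05, σ/δ = 1 and an equal split, 16 patients (32 sites) correspond to 80.7% power; 90% needs 42.03 sites, which is 22 whole patients (44 sites). None of the other readings tried gives 16 patients at 90%. That an 80% result was labelled 90% is the simplest explanation, but the article does not show how the figure arose.

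The consequence at the planned size is modest: about 94% power if all 25 complete and about 88.5% with 20% dropout. The enlargement to 25 largely offsets the shortfall, but for a stated reason that does not hold and is not quantified.

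The conclusion rests on the equal split, which is inferred from the design, and on taking σ and δ as printed. It does not establish that 25 patients are enough for a paired binary non-inferiority comparison.

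**What to change.** In the Sample size section:

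1. State that, on the printed formula and inputs, 16 patients (32 sites) correspond to about 80% power and that 90% needs 22 patients (44 sites).
2. State the power of the planned 25 patients on the same inputs: about 94% if all complete, and about 88.5% if 20% drop out.
3. Delete the clustering rationale and describe the increase from 20 to 25 as a margin.
4. Say that these figures hold only on the printed inputs, where σ is labelled a standard error and the outcome is binary, and say whether σ is a per-side SD or the SD of the paired difference. Apply no (1 − ρ) factor unless it is shown to be the former.

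The cost is one revised paragraph and a slightly less favourable stated power, with no extra patients. Only if the sponsor wished to keep 90% after 20% dropout on these inputs would the number rise, to 28, which is 3 more than planned.

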**Methods/design:**

The study cohort included 25 adult patients (50 surgery sites) recruited from Peking University Hospital and School of Stomatology who met the inclusion criteria. The two sides of each patient will be randomly divided into two groups: a test group-modified MSFE or a control group-standard MSFE. The surgical duration and patient-reported outcomes (visual analog scale for discomfort) will be documented. Clinical indicators, including implant survival rates, mucosal conditions, and complications, will be recorded every 6 months during the 5-year follow-up period. The volume of the alveolar bone and marginal bone level will be assessed radiographically (cone-beam CT and periapical films) every 6 months. Histological analysis of biopsy samples retrieved from both sides will be performed to evaluate the biological features of the bone.

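### The printed sample-size formula and inputs give 42 sites (22 patients) for 90% power; the stated 16 patients (32 sites) correspond to about 80%

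*Protocol article*

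**What the plan says.** The Sample size section of the protocol article bases the calculation on the primary outcome, 5-year implant survival. In ordinary notation the printed formula is N = (1/Q1 + 1/Q2) × [(Z for α/2 + Z for β) × σ/δ]². The inputs are a survival rate of 97.8%, "mean of paired difference [*δ*] = 5.0"%, σ (described as a standard error) also 5.0%, and "significance criteria of *α* = 0.05 (error) and *β* = 0.10 (type II error"). On the test it says: "A two-tailed, non-inferiority analysis was performed".

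The result is "To reach a power of 90%, at least 16 patients (32 sites) should be included". The next step is "Assuming a dropout rate of 20%, 20 patients (40 sites) were needed", and the total is then enlarged to 25 patients (50 sites) to allow for clustering in the split-mouth design. The section defines none of N, Q1 and Q2. On allocation, the abstract says: "The two sides of each patient will be randomly divided into two groups".

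**The concern.** With σ equal to δ the ratio σ/δ is 1, so N depends only on α, β and the allocation factor. This makes the stated 16 patients easy to check, and it does not follow from the stated 90% power. Sixteen is the base for every later figure, so an error there passes into the 20 and the 25. This is also the only power justification the article gives for the primary outcome, in a trial whose hypothesis is that the two procedures give similar results. Readers of a finding of no difference will lean on the stated power.

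**Working it through.** **Inputs (Sample size section unless noted).** σ = 5.0%, δ = 5.0%, so σ/δ = 1. Two-tailed α = 0.05, so Z = 1.960. β = 0.10, so Z = 1.2816; for comparison, β = 0.20 gives Z = 0.8416. The 97.8% survival rate does not enter the formula.

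**Assumptions.** N is total sites, and Q1 and Q2 are the group fractions, each 0.5 because each patient gives one side to each group (abstract, Methods/design). For fractions summing to 1, 1/Q1 + 1/Q2 = 1/(Q1 × Q2), which is smallest at 0.5/0.5, where it equals 4. Any other split raises N.

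**Attempt to reproduce the stated figure at 90% power.** N = 4 × (1.960 + 1.2816)² = 4 × 10.507 = 42.03 sites. That is 21.01 patients: 22 (44 sites) rounded up, or 21 rounded to nearest. The stated figure is 32 sites (16 patients). To obtain 32, the allocation factor would have to be 32/10.507 = 3.05, below its minimum of 4.

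**Same formula at 80% power.** N = 4 × (1.960 + 0.8416)² = 4 × 7.849 = 31.40, which rounds up to 32 sites, or 16 patients. This matches the stated figure.

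**Power implied by the printed formula.** With n sites, power = Φ(√(n/4) − 1.960).

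| Sites analysed | Patients | Power |
|---|---|---|
| 32 | 16 | 80.7% |
| 40 | 20 | 88.5% |
| 44 | 22 | 91.3% |
| 50 | 25 | 94.2% |

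**Drop-out step.** 16/0.8 = 20, so the article's own step is done correctly. From the corrected base, 21/0.8 = 26.25 and 22/0.8 = 27.5, so 27–28 patients. That already exceeds 25 before any enlargement for clustering.

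**Other readings at 90% power.**
- One-sided α = 0.05: 4 × 8.564 = 34.26 sites, 18 patients; 16 patients have 88.2% power.
- Two-sample t: 23 patients.
- Non-inferiority of means at one-sided 0.025: 22 patients.
- Two one-sided tests for equivalence: 22 patients.
- Paired formula with σ as the SD of the paired difference: 10.507, so 11 pairs (z), or 13 (t).

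None of these gives 16.

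**The case against.** The strongest reply is that the planned 25 patients may still be enough on the plan's own terms. Three points support it.

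First, the Missing data section counts drop-outs as non-survival under intention to treat, so they would stay in the analysis. With 50 sites the printed formula gives 94.2%. A reader might infer from the 88.5% that the trial falls short of 90% at 20% drop-out, but that holds only if the lost patients leave the analysis. The point stands, with one limit: counting drop-outs as failures would itself change the difference and its variance, and the Kaplan–Meier and Cox analyses named under Statistical analysis may handle them differently. So 94.2% is not firm either.

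Second, δ is described as a paired difference and the design is split-mouth. If σ belongs to that difference and a paired formula was meant, 16 pairs have 97.9% (z) or 96.2% (t) power. On a one-sided 5% reading, 18 patients are needed, or 23 after drop-out (18/0.8 = 22.5), which 25 covers. Both readings remove a shortfall at 25. Neither is what is printed, however: the formula is the two-group one with α/2, the text says two-tailed, and 16 is the answer to neither.

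Third, Q1, Q2 and N are undefined, so the recalculation rests on an assumption. That is true, but equal allocation is the split most favourable to the stated figure, and reading N as patients instead of sites would move the result further from 16.

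A reader might also infer that the authors ran the software at 80% power. The match is exact after rounding up, but the document does not show how 16 was obtained.

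**Conclusion.** The paragraph is internally inconsistent. On the printed formula and inputs, with N as total sites and equal allocation, 90% power needs 42.03 sites (22 patients rounded up), and the stated 32 sites have 80.7%. The 90% label and the 16 patients cannot both stand.

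The effect on the enrolled number is modest and depends on the reading: 88.5% to 94.2% for 25 patients. The documents do not establish that 25 patients are too few by this route.

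The opposite inference, that 25 are therefore enough, is not supported either. The formula compares means and takes a quantity labelled a standard error as σ, whereas the primary outcome is a binary proportion of retained implants. As an illustration only, a non-inferiority calculation for proportions gives 2 × 0.978 × 0.022 × 10.507/0.05² = 181 per arm. That assumes 97.8% survival in both groups, the 5.0% read as a margin, one-sided 0.025, 90% power and independent arms. This is a separate issue, but it means that the percentages above describe the printed formula and not the trial's power for survival.

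**What to change.** Correct the Sample size paragraph so that formula, inputs, power and N agree, in one of two ways:

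- Keep the printed formula and state its actual output: 16 patients (32 sites) give about 80% power; 90% needs 22 patients (44 sites), or 28 with 20% drop-out; 25 enrolled give about 88% if 20% leave the analysis and about 94% if all are analysed.
- Or print the formula and inputs actually used, with N, Q1 and Q2 defined and the sidedness stated, and show that they lead to 16.

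In either case, label the figures as the output of a mean-difference formula, not as the power for the binary survival outcome, and do not use them to argue that 25 patients are sufficient.

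The cost is one rewritten paragraph. If the first option is taken, the power stated for 16 patients falls from 90% to about 80%. The correction itself changes nothing in the conduct of the trial.
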